#### Exploratory outcomes measures

The functional connection of the corticomuscular closed-loop network (CLN) in the resting and task states will be assessed. This mainly includes the extended partial directed coherence (FCePDC) value between the regions of interest (ROIs) and the small world measurement of the network, such as weighted clustering coefficient, weighted shortest path, and betweenness centrality.

EEG will be acquired according to the international 10–20 system. The Neuroscan system will be used to record the left and right sensorimotor and frontal-parietal cortex EEG. EEG is recorded from 32 Ag/AgCl scalp electrodes (sampling rate of 1000 Hz) using a BrainAmp DC amplifier and an anti-aliasing filter. The electrodes are designated Fz, F4, FC5, FC3, FC1, FCz, FC2, FC4, FC6, C5, C3, C1, Cz, C2, C4, C6, CP5, CP3, CP1, CPz, CP2, CP4, CP6, P3, POz, P4, POz, O1, O2, FCZ (reference), and AFZ (ground). The electrode impedance is kept below 10 kΩ. Some of the electrodes are located on the scalp in the central frontal lobe (FC3, FC4), centre (C3, C4, C5, C6), and the central parietal lobe (CP3, CP4).

EMG will be recorded from signals from the following muscles: the bilateral superior trapezius, anterior deltoid, posterior deltoid, middle deltoid, biceps brachii, triceps brachii, extensor carpi radialis, and flexor carpi radialis. The surface EMG signal will be recorded at 1500Hz through the Noraxon system using disposable Ag-AgCl electrodes with bipolar configuration, with a 2-cm distance between electrodes. After the standard skin preparation procedure, electrode pairs will be placed on each muscle’s abdomen, and the muscle’s surface EMG will be identified by palpation and a few blank tests of elbow flexion and extension. In addition, EMG signals will be monitored online before the experiment to evaluate the positioning and recording quality of the electrodes.

fNIRS uses a continuous wave optical system to measure oxygenated haemoglobin (HbO) in the cerebral cortex. The system’s light source generates near-infrared light (690 nm and 830 nm) at a fixed sampling rate of 10 Hz and a total of 95 channels. A 3D digitizer will be used to obtain the coordinates of the channel. These coordinates will be converted into the MNI coordinates, and then the NIRS_SPM toolbox will be used to project it onto the standard MNI brain model. With the above configuration, the channel can cover the SMA, the PMC, M1, the primary sensory cortex (S1), and the DLPFC.

### fNIRS-EEG-EMG experimental paradigm

There will be three tasks: upper limb forward reach, elbow flexion and extension, and Tai Chi Yunshou. After a 3-min rest period (baseline), the motor paradigm will use a three block design:Upper limb forward reach with three cycles of preparation [3 s] – reach forward [3 s] – rest [3 s];Elbow flexion and extension with three cycles of preparation [3 s] – elbow flexion [3 s] – rest [3 s] – elbow extension [3 s] – rest [3 s];Tai Chi Yunshou with three cycles of preparation [3 s] – Tai Chi Yunshou [3 s] – rest [3 s]

For each motor task, there will be 3 s of preparation. The subjects will be asked to perform specific motor tasks for 3 s according to the instructions and then relax for 3 s. Each motor task will consist of 20 repetitions. The tests will be carried out on both sides of the arm of post-stroke patients. Each subject will use his/her left and right hands to perform each motor task. He/she will take a 5-min break between each task to prevent muscle fatigue. The experiment will last for 30 min for each subject (2 hands × 3 tasks × 20 repetitions). Finally, the static state will be assessed for 3 min. Data will be collected at baseline and after the 4-week intervention.

### Safety evaluation

During the study intervention, any adverse events that occur the subjects will be monitored, recorded on the adverse event case report form (CRF), and then reported to the research assistant. The causal relationship between Tai Chi training and the severity of adverse events will be analysed. Adverse events are defined as any dysfunction caused by the intervention, such as knee or ankle sprain, knee pain, or hypoglycaemia. In the case of any adverse event, the coach or project manager will provide complementary treatment for the participants. Serious adverse events will be reported to the rehabilitation hospital’s ethics committee affiliated with the Fujian University of Traditional Chinese Medicine. Additional file 5 provides additional details.

The safety of subjects will be evaluated based on several factors. The evaluation results are divided into level 1 (safe, no adverse reactions); level 2 (safe but with mild adverse reactions that do not require treatment; subjects can continue to participate in training); level 3 (safety problems and moderate adverse reactions, but the subjects can continue training after receiving treatment); and level 4 (study terminated due to severe adverse reactions) (Common Terminology Criteria for Adverse Events [CTCAE] version 5.0, US Department of Health and Human Services, 2017).

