## Methods/design

### Study design

A randomized, single-blind, parallel-controlled trial will be conducted to evaluate the effectiveness and neural mechanism of traditional Tai Chi training in stroke patients with upper limb dysfunction. The framework of this trial is a superiority trial design. The evaluators and data analysts will be blinded regarding the treatment. A total of 84 eligible participants will be randomly assigned to the Tai Chi group or the control group in a 1:1 ratio. Members of the Tai Chi group will receive 4 weeks of Tai Chi training five times a week, with each session lasting for 60 min (a total of 20 sessions). Participants in the control group will not receive Tai Chi training. Both groups will receive medical treatment and routine rehabilitation training. The primary and secondary outcomes will be measured at baseline and 4 weeks (the end of intervention). This study will use the SPIRIT reporting guidelines [32] (see Additional file 3 for more details). The flow chart of the research design is shown in Fig. 1, and the enrolment, intervention and assessment schedule is shown in Fig. 2. Additional file 4 shows additional details.

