### Sample size estimation

This trial will observe the effects of Tai Chi on upper limb function of post-stroke patients. When calculating the required sample size using the Gpower V.3.1.9.2 software, the Fugl-Meyer Assessment Upper Extremity (FMA-UE) scale served as the primary outcome measure. Based on a published study [33], the FMA-UE scores of stroke patients in the Tai Chi and control groups after intervention were 60.50±2.19 and 59.14±1.77 points, respectively. According to these results, a sample size of 64 participants would be sufficient to detect the target effect size (0.6830377) with a type 1 error of 5% (*α* = 0.05) and 80% power (*β* = 0.20). Assuming a dropout rate of 20%, a total of 84 participants are necessary, with 42 participants in each group.

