#### Dropout criteria

Participants will be withdrawn from the trial for the following reasons:Subjects who experience severe adverse events and are not suitable for the trial;Subjects who suffer another stroke;Subjects who voluntarily withdraw from the trial; Subjects with deterioration or severe complications and who need emergency intervention measures.

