### Intervention

#### Control group

The control group will receive routine medical treatment, health education, and rehabilitation training. According to the 2014 guidelines for the secondary prevention of ischaemic stroke and transient ischaemic attack in China, formulated by the cerebrovascular disease group of the neurology branch of the Chinese Medical Association in 2015, the subjects will receive routine medical care, including aetiological treatment, blood pressure management, antiplatelet therapy, anticoagulation therapy, essential treatment of heart disease, hyperglycaemia treatment, and blood glucose and lipid management. According to published guidelines [34], the following health education will be given to subjects: (1) emphasize the severe harm of stroke so that the patients can consciously take active preventive measures; (2) the principal risk factors and inducing factors of stroke and how to carry out secondary prevention; and (3) coping with stroke and rehabilitation. The therapist will conduct rehabilitation training for the subjects according to the guidelines [35]. The participants will receive rehabilitation treatment by trained occupational therapists for the affected upper limb; it will consist of five 60-min sessions per week, for a total of 20 total sessions.

During the entire 4-week intervention, all subjects will record the duration of activities each day (classified as static work, low-intensity activity, medium-intensity activity, and high-intensity activity), their diet, and the drugs they take.

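### The adverse event definition requires causation by the intervention, so unattributed events in either arm are not counted and any comparison of harms is open to bias

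*Protocol article*

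**What the plan says.** Four statements in the Safety evaluation section bear on this point.

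- Recording: "During the study intervention, any adverse events that occur the subjects will be monitored, recorded on the adverse event case report form (CRF"). No arm is excluded.
- Planned analysis: "The causal relationship between Tai Chi training and the severity of adverse events will be analysed".
- Definition: "Adverse events are defined as any dysfunction caused by the intervention, such as knee or ankle sprain, knee pain, or hypoglycaemia".
- Grading: four levels built on adverse reactions and on whether training can go on, for example "level 2 (safe but with mild adverse reactions that do not require treatment; subjects can continue to participate in training").

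The same section sends serious adverse events to the hospital's ethics committee and names the coach or project manager as giving treatment when an event occurs. It refers to Additional file 5 for more detail. That file is not shown, and the recruitment section identifies it as the consent form.

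Elsewhere, Study design says: "Participants in the control group will not receive Tai Chi training". The control arm is nevertheless described under the Intervention heading: "The control group will receive routine medical treatment, health education, and rehabilitation training". The Dropout criteria list "Subjects who suffer another stroke" as a reason for withdrawal separate from severe adverse events, and do the same for deterioration or severe complications. No section shown defines an adverse event without reference to its cause.

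**The concern.** A randomised comparison of harms works because events are counted in the same way in both arms, whatever anyone believes about their cause. Here attribution comes first: it decides whether an event enters the count at all. That has three consequences.

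- Unattributed events are lost in both arms. Depending on how attribution is made, this can hide a real excess or create a false one.
- The restriction carries over to serious events, because the ethics committee route uses the same defined term.
- The plan to relate Tai Chi to adverse events sits badly with the definition. A set selected on attribution cannot show whether Tai Chi makes such events more frequent.

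Participants are aged 50 to 70 and enter between 2 weeks and 6 months after a first stroke, so events unrelated to training are to be expected. The Discussion looks for a safe, low-cost treatment and for its wider use in hospitals, communities and families. A safety claim of that kind needs comparable counts from the two arms.

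**Working it through.** **Text check.** The plan states no figure on this point, so there is nothing to reproduce. The passages are taken in turn.

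1. *Does the recording sentence repair the definition?* It covers any adverse event in the subjects, but it uses the term that the definition restricts. Read together, what must be recorded is any dysfunction caused by the intervention.
2. *What does the intervention mean?* On the narrow reading (Tai Chi only) the pointers are the Tai Chi causality sentence, the coach's role and grading by continued training. Controls receive no Tai Chi, so none of their events can qualify. On the broad reading (whatever the assigned arm receives) the pointers are the Intervention heading over the control arm and a sentence there that refers to the 4-week intervention for all subjects. Control events attributed to routine care could then qualify. Unattributed events are lost on both readings.
3. *Can the planned analysis still be done?* It literally concerns severity, which can vary among attributed events. Occurrence cannot be studied, because every event in the set has already been judged to be caused by the intervention.

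**Illustration of size (assumed rates, narrow reading).**

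Inputs: n = 42 per arm, from Sample size estimation ("a total of 84 participants are necessary, with 42 participants in each group"). Assumed: the same true any-cause risk p in both arms, and a fraction f of Tai Chi events attributed. A between-arm two-sided Fisher exact test at 0.05 is also assumed; the plan states no such test for harms.

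- True expected participants with an event, per arm: 42 × p.
- Counted in controls: 0. Counted in the Tai Chi arm: X ~ Binomial(42, p × f).
- Fisher threshold against 0 of 42: 5 v 0 gives P = 0.055 and 6 v 0 gives P = 0.026, so significance needs X ≥ 6.
- Chance of a false difference: P(X ≥ 6).

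| p | True expected per arm | f = 0.5 | f = 1 | All events counted in both arms |
|---|---|---|---|---|
| 5% | 2.1 | 0.1% | 1.7% | 0.5% |
| 10% | 4.2 | 1.7% | 24% | 1.8% |
| 20% | 8.4 | 24% | 87% | 2.9% |
| 30% | 12.6 | 62% | 99.5% | 3.0% |

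In plain counts, also assumed: if 10 events occurred in each arm and 60% of those in the Tai Chi arm were attributed, 10 × 0.6 = 6 would be reported against 0, when the truth is 10 against 10. In the other direction, if none were attributed, a true excess would be reported as zero.

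**The case against.** The strongest reply is that the sentence is loosely worded and that practice will be sounder. Recording is promised for the subjects without restriction by arm, and the causality analysis is placed after recording, which suggests that events are written down before anyone judges their cause. This is plausible as intent. It does not rescue the text, because the recording sentence depends on the defined term.

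Some stronger inferences are tempting, and the objection is right to resist them.

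- *All control-arm events are lost.* This holds only on the narrow reading. The article also uses the word intervention for what both arms receive.
- *An unblinded person decides what counts.* The document does not say who attributes cause. Assessors collect the data and are blinded; coaches and participants are not. Biased attribution is possible, but it is not stated.
- *The causality analysis is wholly circular.* Its wording concerns severity, which is not fixed by the definition. The conflict is with learning about occurrence.
- *Recurrent strokes would vanish.* They are a withdrawal reason in either arm whatever the cause, so they would still appear as withdrawals. The risk of going unseen falls mainly on lesser unattributed events.

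It is also fair that the event rates above are assumed, that safety is not a primary or secondary outcome, and that case report form layout and analysis detail may be set out in documents not shown. What stands is the definition itself. It is a stated rule, not an omitted detail, and a definition that ignored cause elsewhere would contradict it.

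**Conclusion.** The point holds as a defect in the stated definition. Followed as written, the plan leaves out events not attributed to the intervention in both arms, gives unattributed serious events no stated route to the ethics committee, and cannot show whether Tai Chi raises the occurrence of adverse events. Confidence in this is high, because it rests on the wording alone.

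The complete absence of a control rate is conditional on the intervention meaning Tai Chi. The section favours that reading but does not fix it.

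The size is unknown. Under the narrow reading and assumed equal risks of 5% to 30%, the chance of a false difference runs from about 0.1% to 62% if half of the Tai Chi events are attributed, and from about 2% to 99.5% if all are, compared with 0.5% to 3% under neutral counting. These figures show that the problem grows quickly with the event rate; they do not predict this trial. The efficacy analysis and the sample size are unaffected. The change should be made.

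**What to change.** - Define an adverse event as any untoward medical occurrence in either arm from randomisation to the week-4 assessment, whatever its cause, and let serious adverse event reporting follow the same definition.
- Collect events in the same way in both arms on the existing adverse event form. Both arms attend 20 rehabilitation sessions and keep daily records, so equal collection is practicable.
- Record relatedness and severity as separate items after the event has been entered, and state who judges relatedness.
- Report the number and proportion of participants with any adverse event and with any serious adverse event by randomised arm.

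The cost is a revised definition through the article's amendment route and a few more events to record. Treatment, sample size and efficacy analysis do not change. There is a transition cost: the trial began in March 2022, this version is dated October 2023 and completion is hoped for by December 2024. Participants followed under the old definition should be identified, their withdrawal records reviewed for missed events where possible, and the change of definition and its date reported with the safety results.

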#### Tai Chi group

This group will receive Tai Chi training, routine medical care, health education, and rehabilitation training. The routine care, education, and rehabilitation training will be the same as described for the control group. The Tai Chi training will be led by Tai Chi coaches with more than 5 years of qualification. Tai Chi training follows a gradual process from part to whole and from easy to complex. The teacher will choose the appropriate form of Tai Chi according to each participant’s ability. When adjusting Tai Chi training for each participant, two fundamental principles are used: (1) the participant should be able to practice Tai Chi while relaxing and (2) there should be as much overall coordination as possible. The participant relaxes his/her muscles and joints as much as possible and focuses on movements that help him/her relax, completing these movements with minimal effort. The movement is slow, repetitive, and, if necessary, carried out in sections. Eight Tai Chi poses will be adopted in this study: Starting Posture, Parting the Wild Horse’s Mane on both sides, Brush Knee and Twist Step on both sides, Forearm Rollings on both sides, Grasp the Bird's Tail – Left Side, Grasp the Bird's Tail – Right Side, Cloud Hands, and Closing Form. These poses have been selected based on the literature [4, 36]. Please refer to 24 simplified standard movements of Tai Chi promoted by the General Administration of Sport (http://www.sport.gov.cn/). In the actual training process, the accuracy and consistency of the posture routine will not be emphasized. At the same time, according to the actual movement ability of the patient, the difficulty of reaching the posture standard will be appropriately reduced. The participants will receive five 60-min sessions per week, for a total of 20 sessions. Each session will include 5 min of warm-up, 50 min of Tai Chi training, and 5 min of cooldown. The training will be conducted at Fujian provincial rehabilitation hospital. The researchers involved in this trial will not carry out relevant concomitant care and interventions that are permitted or prohibited during the trial.

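### The safety levels tie severity to whether the participant continues, so a severe reaction in someone who stays in the trial fits no level

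*Protocol article*

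**What the plan says.** The Safety evaluation section of the protocol article sets four levels. Level 1 means no adverse reaction. Level 2 is for "mild adverse reactions that do not require treatment; subjects can continue to participate in training". Level 3 is "level 3 (safety problems and moderate adverse reactions, but the subjects can continue training after receiving treatment". Level 4 is "level 4 (study terminated due to severe adverse reactions". CTCAE version 5.0 is cited directly after the list. The same section defines adverse events as dysfunction brought about by the intervention, "such as knee or ankle sprain, knee pain, or hypoglycaemia", and states: "The causal relationship between Tai Chi training and the severity of adverse events will be analysed".

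The Dropout criteria section lists four grounds for withdrawal. The one that bears on the levels is the first: "Subjects who experience severe adverse events and are not suitable for the trial".

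**The concern.** A severity scale should give every event a place, and that place should depend on how severe the event was. Here each level from 2 to 4 also carries a statement about what happens to the participant. The top level is reached only when a severe reaction ends participation, yet the first withdrawal rule appears to let some participants with a severe event remain.

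If such a case arises, the person completing the form has no correct level to enter. Level 3 is the nearest, because its second half (continuing after treatment) fits, but its first half says moderate. A severe reaction entered there, or left without a level, drops out of the level 4 count, which is the category a safety reader looks at first.

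**Working it through.** The protocol gives no figure to reproduce, so the check sets the two sections side by side.

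**How the terms are read.**
- The levels rate the safety of individual subjects, so termination in level 4 is taken to mean that the participant stops, not that the whole trial closes.
- Dropout criteria speaks of adverse events and the levels speak of adverse reactions. Safety evaluation defines adverse events as caused by the intervention, so the two terms overlap for this purpose.

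**Step 1: cross severity with continuation, using the level definitions.**

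| Severity | Participant can continue | Participant stops or cannot train |
|---|---|---|
| None | Level 1 | not applicable |
| Mild | Level 2 | no level |
| Moderate | Level 3 | no level |
| Severe | no level | Level 4 |

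Levels 2 and 3 also carry a condition about treatment, which the table leaves out. Adding it would narrow those definitions further and would fill none of the empty cells.

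**Step 2: ask which empty cells the protocol makes possible.**
- *Severe, continues.* The first withdrawal rule has two parts joined by a conjunction: a severe adverse event, and unsuitability for the trial. The second part would be redundant unless some participants with a severe event remain suitable. No other section requires every participant with a severe reaction to stop. The withdrawal rules therefore leave this cell open. Level 3 does not take it (not moderate) and level 4 does not take it (no termination).
- *Moderate, stops.* Sprains of the knee or ankle are among the protocol's own examples of adverse events, and the Tai Chi programme includes stepping poses such as "Brush Knee and Twist Step on both sides". A sprain of moderate severity that prevents further training is plausible, although no section describes one. Level 3 requires that training can go on, and level 4 requires a severe reaction.
- *Mild, stops.* This cell is empty on the wording, but a mild reaction that itself prevents training is a strained case and the point does not rest on it.

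A participant who chooses to leave after a mild or moderate reaction is not a gap, because levels 2 and 3 speak of being able to continue.

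**Step 3: consequence for the count.** Read literally, level 4 counts severe reactions that ended participation. That is a subset of all severe reactions, so the count can be too low as a measure of severe reactions but not too high.

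**The case against.** Continuation after a severe reaction is inferred, not stated. The words about unsuitability could describe the result of a severe event instead of a second condition, and Safety evaluation pairs severe reactions with termination only. On that reading the main gap closes. The reading is possible, but it makes the second half of the rule idle, so the two-part reading is the plainer one. The moderate reaction that stops training would remain uncovered either way.

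It can also be said that the levels are an overall safety rating meant to combine several factors, that the article does not say they are the variable in the planned severity analysis, and that CTCAE is cited beside them. This stands in part: the link between levels and analysis is not explicit. But the printed level definitions still add continuation or stopping conditions, and a composite rating also needs a place for every case.

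The case report form and Additional file 5 are not shown and may already grade severity separately. That would reduce the repair to one sentence.

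A reader might infer three stronger points, which the documents do not support:
- *A second withdrawal rule opens the same gap.* The rule "Subjects with deterioration or severe complications and who need emergency intervention measures" has a similar form, but it need not concern reactions to the intervention. The exclusion criteria use like wording for complications of stroke, which the safety levels do not grade.
- *Equal severity will be graded differently in the two arms because coaches and participants know the treatment.* The Blinding section keeps evaluators blind to assignment, Outcome measurements says the same of assessors, and no section says who assigns the level or decides on stopping. Differential grading is conjecture.
- *The shortfall can be expressed as a percentage per arm.* That would need an assumed number of severe reactions in continuing participants, and the article gives no event rate.

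**Conclusion.** The point holds as a minor defect in a stated rule. Levels 2 to 4 mix severity with action taken, and on the plain reading of the first withdrawal rule a severe reaction in a continuing participant has no level. A moderate reaction that stops training has none either. The level 4 count can therefore understate severe reactions.

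This rests on three assumptions: the withdrawal rule states two separate conditions, termination in level 4 refers to the participant, and the case report form does not already grade severity apart from action. The number of participants affected cannot be derived from the document and may be nil. The reach is limited to classifying and tabulating safety. The efficacy outcomes, sample size and error rates are untouched.

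**What to change.** Keep level 1 for no reaction and assign levels 2, 3 and 4 by the participant's worst severity alone (mild, moderate, severe), whether or not participation stops. Take severity from the CTCAE version 5.0 criteria already cited. On the adverse event form, record treatment given (yes or no) and action on participation (continued, interrupted, stopped) as separate items in both arms. Use the severity grade in the planned severity analysis and report it by arm.

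If the case report form or Additional file 5 already grades severity separately, it is enough to say in Safety evaluation that this grade is the one analysed.

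The cost is a small rewording of Safety evaluation, two items on the form, one safety table, and re-coding of events recorded since the trial started in March 2022. No visits or participants are added.
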